### 2.10. Sample Size Calculation

This study was not intended to evaluate the effectiveness of acupuncture treatment but rather to evaluate the suitability of various sham devices. Therefore, we did not follow the general method for obtaining the sample size. The target number of participants in this study was selected on the basis of the number of participants in the previous study [14], which was a sham acupuncture comparison study conducted in healthy individuals [14]. In the previous study, the participants were divided into verum acupuncture, Park Sham Device, Needle + Foam, Insertion and Removal, Real + Park Sham device, Real + Needle + Foam, and Real + Insertion and Removal groups. Twenty-two participants per group were recruited. Therefore, on the basis of this, we decided to recruit at least 22 participants for each group and to recruit 90 stroke patients considering withdrawal during the trial.

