**Methods:**

The proposed study is a single-center, prospective, randomized sequence, participant- and assessor-blinded trial with four parallel arms. A total of 90 participants will be randomly assigned to Group 1, Group 2, Group 3, or Group 4 in a 1 : 1 : 1 : 1 ratio. All groups will be treated with Quchi (LI11) for 20 minutes. Group 1 will be treated with verum acupuncture; Group 2, with Park Sham Device; Group 3, with Streitberger's needle; and Group 4, with insertion- and removal-type devices. Participants will undergo one treatment session. The primary outcome is Bang's blinding index. Secondary outcomes are the “Discomfort caused by acupuncture therapy” questionnaire and the Massachusetts General Hospital Acupuncture Sensation Scale index. Immediately after the procedure, all participants will also be monitored for adverse events.

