### 2.5. Randomization and Allocation Concealment

After registration, the participants will be randomized to Group 1, Group 2, Group 3, or Group 4. Group 1 will receive verum acupuncture; Group 2 will receive Park Sham Device acupuncture; Group 3 will receive Streitberger's needle acupuncture; and Group 4 will receive insertion- and removal-type acupuncture. In this allocation, the stratified-block randomization will be conducted by an independent CRC. The stratification is performed according to whether there is a sensory disturbance of the affected limb (1: no sensory disturbance; 2: sensory disturbance). Block lengths are eight. Random assignment will be conducted by computer-based randomization. The block random function of R software (version 3.1.2) will be used to generate a random number. The assignment probability of the treatment group and the three control groups is 1 : 1 : 1 : 1. For allocation concealment, an independent CRC places the random assignment code in an impermeable envelope and seals it, and it is then delivered to the practitioner. The practitioner will open the random assignment envelope in front of the participant and assign the participant. After that, practitioners will keep the opened envelopes with themselves.

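### The total of 90 does not guarantee the stated minimum of 22 per group, and its reserve for withdrawal is two patients in the whole trial

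*Protocol article*

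**What the plan says.** Section 2.10 (Sample Size Calculation) states that the usual route was not taken: "we did not follow the general method for obtaining the sample size". The group size comes from an earlier sham-comparison study in healthy people, of which it says "Twenty-two participants per group were recruited". From this it sets a floor and a total: "we decided to recruit at least 22 participants for each group and to recruit 90 stroke patients considering withdrawal during the trial". No withdrawal rate is given.

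The Methods paragraph of the abstract treats 90 as the number randomised: "A total of 90 participants will be randomly assigned to Group 1, Group 2, Group 3, or Group 4", in equal ratio. Section 2.5 stratifies by presence or absence of sensory disturbance in the affected limb and adds "Block lengths are eight". The article mentions no cap on a stratum, no replacement of patients who withdraw, and no rule to continue until each arm holds 22.

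**The concern.** A floor per group, a total and a randomisation scheme are all stated, so they can be checked against each other. The total exceeds four times the floor by only two patients, 90 does not divide evenly by four, and two strata with blocks of eight will always leave at least one block unfinished.

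Because no formal calculation was made, 22 per group is the only justification offered for the size of the trial. Section 2.11 reports the primary outcome, Bang's blinding index, for each group, so the smallest arm limits what can be said about its device. If arms of 20 or 21 appear in the final report, they may be taken for a recruitment failure when they were a foreseeable result of the design.

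**Working it through.** **Inputs from the article.** Floor 22 per group and total 90 (2.10); four arms, ratio 1:1:1:1, two strata, blocks of eight, hence two places per arm per block (2.2 and 2.5).

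**Assumptions, not in the article.** Sensory disturbance in 20% to 50% of patients; withdrawals at random; withdrawal rates of 0%, 2.2% and 5% for illustration.

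**1. The plan's own figure.** 4 × 22 = 88 and 90 − 88 = 2. An allowance of 2/90 = 2.2% reproduces the 90 (88/0.98 = 89.8, rounded up to 90). The total is therefore explained as floor plus a reserve of two.

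**2. Does the reserve protect the floor?** 90/4 = 22.5, so the most even split is 22/22/23/23 and two arms have no spare patient.
- One random withdrawal keeps every arm at 22 only if it falls in an arm of 23: 46/90 = 0.51. The floor is broken with probability 44/90 = 0.49.
- Two withdrawals keep it only if one falls in each arm of 23: (23 × 23)/4005 = 0.13, where 4005 is the number of pairs among 90.
- Three withdrawals leave 87, which is fewer than 88, so the floor cannot hold.

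**3. Blocks, before any withdrawal.** 90 = 11 × 8 + 2, so the patients in the two unfinished blocks (the stratum remainders modulo 8) add to 2 or to 10.
- Sum 2 (0+2, 1+1, 2+0): eleven full blocks, every arm at least 22.
- Sum 10 (3+7, 4+6, 5+5, 6+4, 7+3): ten full blocks, 20 per arm, with the other ten patients in two partial blocks.

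An arm stays at 20 only if it is absent from both partial blocks. For 5+5 the chance that a given arm is absent from the first five places of a block is C(6,5)/C(8,5) = 6/56; squared and multiplied by four arms this is 0.046. For 4+6 it is 4 × (15/70) × (1/28) = 0.031. For 3+7 an arm cannot be absent from seven of eight places, so the smallest possible arm is 21.

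| Remainders | Smallest arm 20 | Smallest arm 21 | Smallest arm 22 |
|---|---|---|---|
| 0+2, 1+1, 2+0 | 0 | 0 | 1 |
| 3+7, 7+3 | 0 | 0.357 | 0.643 |
| 4+6, 6+4 | 0.031 | 0.437 | 0.533 |
| 5+5 | 0.046 | 0.444 | 0.510 |

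With the eight remainder patterns about equally likely:
- P(smallest arm 20) = (2 × 0.0306 + 0.0459)/8 = 0.013
- P(smallest arm 21) = (2 × 0.3571 + 2 × 0.4367 + 0.4439)/8 = 0.254
- P(some arm below 22) = 0.267

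Exact weighting by a binomial stratum split gives 0.264 to 0.268 for prevalences of 20% to 50%. The largest possible arm is 24.

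**4. Blocks and withdrawals together.** The expected smallest evaluable arm is about 21.7 at 0% withdrawal, 20.9 at 2.2% and 20.0 at 5%.

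**5. What this costs in precision.** For one arm the variance of the index is largest at an index of 0 with no do-not-know answers, where it is 1/n. The 95% half-width is then 1.96/√n: 0.418 at n = 22 and 0.438 at n = 20, a difference of 0.02 on a scale from −1 to 1.

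**The case against.** The strongest case on the other side has four parts.

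- **The 22 may be a recruitment target.** The earlier study's 22 was also a number recruited. If the floor counts patients allocated, withdrawals cannot breach it. This stands as a possible reading. It removes the withdrawal point but not the block point, and it leaves the mention of withdrawal in 2.10 without a function.
- **Losses may be very few.** Treatment is one 20-minute session in inpatients, the envelope is opened in front of the participant, and the questionnaires follow immediately. This also stands: an allowance near 2% is thin, but the article does not show it to be wrong, and the 5% rate used above is only an illustration.
- **A condensed article may leave replacement rules to the full protocol.** This is fair, and the absence of such a rule is not held against the plan. But the abstract fixes the number randomised at 90, and replacing patients would exceed it.
- **Nothing formal depends on 22.** No power or precision claim is attached to it, so a shortfall of one or two patients changes no conclusion. This stands and keeps the point small.

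A reader might infer more: that 90 fails to provide 22 per group, that an arm of 20 is to be expected, or that the trial is too small as a result. The documents do not support any of these. Before withdrawals every arm reaches 22 in about 73% of allocations, 20 is a rare extreme, and the loss of precision is slight.

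**Conclusion.** The point holds as a mismatch between stated figures: a total of 90 guarantees neither a minimum of 22 in every group nor a working reserve for withdrawal. The reserve of two patients and the possible range of 20 to 24 per arm follow from the article's own numbers. The 27% chance of an arm below 22 without withdrawals assumes that a final incomplete block is left unfilled in each stratum and depends very little on the assumed prevalence of sensory disturbance. The figures after withdrawal depend on assumed rates and on reading 22 as evaluable patients. The consequence is modest, at most about 0.02 in the half-width between 22 and 20 patients, but the wording is inaccurate and cheap to correct.

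**What to change.** Reword the last sentence of 2.10 without changing the number of patients, for example:

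> Ninety patients will be randomised, giving 20 to 24 per arm (usually 21 to 23). Twenty-two per arm is a target, not a guaranteed minimum, and the total leaves a reserve of only two patients.

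Say whether the 22 counts allocated or evaluable patients. Then add two items:
- the expected smallest evaluable arm over withdrawal rates labelled as assumptions: about 21.7 at 0%, 20.9 at 2.2% and 20.0 at 5%;
- the 95% half-width of the per-arm index, about 0.42 with 22 patients and 0.44 with 20, labelled as the worst case (index 0, no do-not-know answers).

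The cost is a few sentences and no added patients or procedures. The downside is that the stated size looks slightly less favourable. If the sponsor wants a true floor at allocation, 94 is the smallest total that secures 22 per arm for every stratum split under the present scheme, before any withdrawal. The correction does not require that increase.

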### 2.11. Statistical Analysis

Hypothesis to be tested in this study is that the certain sham device will reveal the most similar sensation to verum acupuncture in the affected limb of stroke patients. Primary outcome of this study is Bang's blinding index in each group. The value of Bang's blinding index of each sham acupuncture device will be calculated by comparison with the verum acupuncture group. This statistical process will be based on Bang's previous study, published in 2004 [18]. In secondary outcome analysis, the values of “Discomfort caused by acupuncture therapy” five questions and MASS index will be compared by ANOVA. In baseline characteristics, categorial variables will be compared by a chi-square test and continuous variables will be compared by ANOVA. A comparative analysis of the frequency of patients with sensory disturbances by each group will evaluate whether stratification assignments have been made properly. In subgroup analysis, we will compare the values of primary and secondary outcomes in patients with sensory disturbances. Patients with sensory disturbances are defined as patients who complaint sensory disturbances such as numbness, hypesthesia, or paraesthesia in affected limbs. In this study, sensitivity analysis will not be performed. A 5% significance level will be used. Study data will be analyzed using the Statistical Package for the Social Sciences (SPSS) software, version 16.0, for Windows and Microsoft Excel 2010 for windows by a blinded statistician.

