**Discussion:**

This study will help identify the optimal sham acupuncture device that can be used for clinical studies on acupuncture treatment in hemiplegic stroke patients. This trial is registered with KCT0002622.

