### 2.8. Outcome Assessments

#### 2.8.1. Primary Outcome

Immediately after the end of the procedure, a questionnaire will be administered to assess the success of blindedness, and the results were used to obtain Bang's blinding index (BI) [18]. The questionnaire is organized as follows: (i) strongly believe the treatment is verum acupuncture, (ii) somewhat believe the treatment is verum acupuncture, (iii) somewhat believe the treatment is sham acupuncture, (iv) strongly believe the treatment is sham acupuncture, and (v) do not know. The BI value ranges from −100 to 100%. A value of 0% represents random guessing (for example, 50% accurate and 50% inaccurate), 100% represents complete unblinding (for example, all answers are accurate), and −100% represents the opposite of guessing (for example, all responses are incorrect).

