## 3. Discussion

There is a limitation in this study. All subjects receive only one acupuncture treatment. Most acupuncture clinical trials involve several acupuncture treatments. Therefore, the present study cannot provide insights into the maintenance of blinding over the course of treatment time. Second, the design of this study cannot compare the effects on stroke of three sham acupuncture devices. This design can only evaluate the sensation after puncture of subjects. The effect on the disease is also important for sham acupuncture devices. However, we will not be able to evaluate this point in this study. Third, this study will be conducted as a single center trial.

However, this study would be meaningful in the following points. This study will provide evaluation results on the optimal sham acupuncture device that can be used for clinical studies on acupuncture treatment in hemiplegic stroke patients. The results of this study will be useful for standardizing clinical studies on hemiplegic stroke-related acupuncture in the future. If there are more clinical studies using the same and optimal sham acupuncture device in the future, it will be possible to obtain more definite results than those from the present systematic review and meta-analysis, which comprehensively evaluate the clinical effects of acupuncture in patients with hemiplegic stroke. The results of this study will be published regardless of the outcome, in accordance with the STRICTA guidelines.

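### Section 2.11 states a most-similar-to-verum hypothesis, but the sensation outcomes get only an ANOVA for difference, and nothing stated leads to the promised optimal device

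*Protocol article*

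**What the plan says.** Section 2.11 (Statistical Analysis) gives the hypothesis: "Hypothesis to be tested in this study is that the certain sham device will reveal the most similar sensation to verum acupuncture". The outcomes that measure sensation are secondary, and for them the section says that the "five questions and MASS index will be compared by ANOVA". It adds: "A 5% significance level will be used".

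The primary outcome is Bang's blinding index: "The value of Bang's blinding index of each sham acupuncture device will be calculated by comparison with the verum acupuncture group". The calculation follows a cited 2004 method paper. Section 2.8.1 anchors the scale ("A value of 0% represents random guessing", with the extremes at 100% and −100%) but gives no range that would count as acceptable blinding.

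Section 2.10 says that the usual sample size method was not followed. It takes at least 22 per group, 90 in total, from an earlier study in healthy people.

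On the conclusion, the abstract says: "This study will help identify the optimal sham acupuncture device". Section 3 says: "This study will provide evaluation results on the optimal sham acupuncture device", and hopes that this will help standardise later stroke trials.

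**The concern.** Hypothesis, method and conclusion do not fit together. ANOVA asks whether group means differ. A non-significant result is not evidence that a sham feels like verum, and a significant overall result does not show which sham is closest. Most similar is also not falsifiable as worded: one of three devices always has the smallest observed difference from verum, even if all three are identical.

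The primary index does not close the gap. The article states no band around 0, no comparison of one sham with another, and no rule that leads from three indices to one preferred device. The device named may become the comparator in later stroke trials, so a choice resting on sampling variation would be carried forward.

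**Working it through.** **The plan's own figure.** 4 × 22 = 88, so 90 leaves 2 spare. No power, effect size, SD or margin is given, so there is nothing further to reproduce. Below, n = 22 per arm and alpha = 5% come from the article. Two-sided testing, SD = 1, the effect sizes, the margins and the 'do not know' rates are assumptions.

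**1. ANOVA on a sensation score, one arm shifted by 0.5 SD.** Means (0, 0, 0, 0.5), grand mean 0.125.
- Sum of squared deviations: 3 × 0.125² + 0.375² = 0.1875.
- Effect size f = √(0.1875/4) = 0.217; noncentrality 22 × 0.1875 = 4.125.
- Critical F(3, 84) = 2.713, so power = 0.353. The shift is missed in about 65% of trials.
- Range: power is 15% at 0.3 SD and 76% at 0.8 SD.

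**2. Precision of one sham-verum difference in means.** SE = √(2/22) = 0.302 SD. The 95% half-width is 2.018 × 0.302 = 0.61 SD.

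**3. Precision of one arm's Bang index.** Variance = (P(correct) + P(incorrect) − BI²)/n. At BI = 0 with no 'do not know' answers, SE = √(1/22) = 0.213 and the 95% half-width is 1.96 × 0.213 = 0.42. With 40% 'do not know' it is 0.32.

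**4. Three identical shams, true index 0 (simulation).** The largest and smallest observed indices differ by 0.36 on average with no 'do not know' answers, and by 0.32 with 20%.

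**5. Picking the index closest to 0 (simulation; true indices 0, g, g).** The article does not state this rule. It is used only to gauge how well 22 per arm can rank devices. Chance is 33%.

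| g | Right device, no 'do not know' | Right device, 20% 'do not know' |
|---|---|---|
| 0.2 | 45% | 48% |
| 0.3 | 59% | 64% |
| 0.5 | 86% | 92% |

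**6. What a similarity claim would need (two one-sided 5% tests, true difference 0).** Power at 22 per arm = 2Φ(margin/0.302 − 1.645) − 1, set to 0 where this is negative.
- 0.3 or 0.4 SD: 0%.
- 0.5 SD: about 1%.
- 0.6 SD: 27%.
- 0.8 SD: 69%.

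For 80% power at 0.5 SD, n = 2 × ((1.645 + 1.282)/0.5)², which rounds up to 69 per arm.

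**7. Unadjusted comparison of shams.** With three identical devices there are three pairs. At least one unadjusted 95% CI excludes 0 in about 12% of trials per outcome, so any rule of this kind needs adjustment.

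**The case against.** Several points on the other side stand.

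- **Primary outcome.** A reader might infer that the only inference in the plan is a difference test. The article does not support that: it names no test for Bang's index and defers to a cited method that is not at hand, read on a scale anchored at 0%.
- **Reading of non-significance.** A reader might infer that a non-significant ANOVA will be taken as similarity. No section says so. The risk arises because no other route from ANOVA to most similar is stated.
- **Comparison of devices.** It would be wrong to say that the shams are never compared. The ANOVA includes all groups. What is absent is a named contrast or selection rule, which an article may leave to a fuller plan.
- **Selection by chance.** The closest-to-0 rule in the working is an illustration. It is also not the same as being most like verum: if 75% of verum and 50% of sham recipients believe they had verum, with no 'do not know' answers, the sham index is 0 although belief differs by 25 points. Selection improves quickly as the true gap grows.
- **Tone.** Section 2.1 speaks of exploring, and the abstract only of helping to identify.

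None of this removes the mismatch. The hypothesis, the ANOVA and the promised conclusion are all in the article, so they can be judged without a fuller plan.

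**Conclusion.** The concern holds in this form: the hypothesis is greatest similarity in sensation; the only method named for sensation tests for difference; and for the primary index the article gives neither a between-device comparison nor an acceptance band, while promising an optimal device.

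At 22 per arm the consequence is material for small to moderate differences. A 0.5 SD shift goes undetected in about 65% of trials, and true index gaps of 0.2 to 0.3 lead to the right choice in only about 45% to 59%. It is much smaller for large ones: 86% correct at a gap of 0.5. To say that a device would simply be named from noise therefore goes too far, because that depends on true differences nobody yet knows. All these figures rest on assumed effects and, for the index, on assumed rates of 'do not know' answers. The mismatch itself rests on the text alone.

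**What to change.** - Reword the hypothesis in 2.11 as exploratory estimation of how close each sham is to verum.
- Report each arm's Bang index, and each sham-verum difference in belief, the yes/no items, discomfort intensity and MASS, with 95% CIs.
- Compare the shams with each other by multiplicity-adjusted CIs. Call one device more suitable than another only if the adjusted CI for their difference excludes 0. Otherwise conclude that the devices could not be separated.
- State that a non-significant ANOVA will not be read as similarity.
- If a similarity claim is kept, fix the margin before unblinding. State that margins of about 0.5 SD or less cannot be met with useful probability at this size.
- In the abstract and section 3, replace the promise of an optimal device with an estimate of how close each device is to verum.

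The change affects wording and reporting and adds no participants. Its price is a weaker conclusion: the trial will often have to say that no device is clearly best. A similarity claim at 0.5 SD would not be a wording change, since it needs about 69 per arm.

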In most clinical studies in stroke patients, acupuncture treatment is usually applied to the paralyzed acupoint. However, the paralyzed limbs of stroke patients have complex patterns of muscle tone, muscle strength, and sensory abnormality [17], and there could be differences in the degree of sensitivity during stitching and the discomfort felt during acupuncture treatment compared to those in healthy individuals. Therefore, it is difficult to apply the validation results of sham acupuncture treatments, evaluated in healthy individuals, to stroke patients. However, there has been no study that has evaluated which type of sham acupuncture is suitable for a study population of stroke patients. In addition, even in acupuncture-related clinical trials involving similar stroke types, there are limitations to performing a meta-analysis because of the different types of sham acupuncture treatments used in each study.

In this study, we will evaluate the success rate of blindness and the posttreatment response to sham acupuncture treatments (three types) compared with verum acupuncture treatment in hemiplegic stroke patients. To assess the success blinding rate of various sham acupuncture treatments, a randomized, double-blinded (participants and evaluator), 4 group paralleled clinical trial will be conducted. Through this study, we aim to explore the most appropriate sham acupuncture tool for clinical research on stroke.

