### 2.3. Inclusion and Exclusion Criteria

Participants who meet the following criteria will be included: (1) 19 years or older; (2) diagnosed with cerebral hemorrhage or cerebral infarction through brain computed tomography (CT) or magnetic resonance imaging (MRI); (3) weakness or hemiparesis or hemiplegia due to cerebral hemorrhage or cerebral infarction, with a Modified Ashworth Scale (MAS) score of 2 points or less; (4) stable vital signs; and (5) voluntary participation in this study.

The following participants are excluded: (1) patients with unconsciousness, aphasia, and cognitive dysfunction (Mini-Mental State Examination-Korean version (MMSE-K) <24); (2) those with a past history of brain disease (e.g., previous stroke, mental illness, consciousness disorder due to head trauma, previous brain surgery, or spastic disease); (3) those with severe heart, liver, or kidney disease or bleeding disorders; (4) those with other serious diseases (e.g., cancer, dementia (Alzheimer's disease or dementia of Lewy body), Parkinson's disease, and Parkinson's syndrome); (5) those with subarachnoid hemorrhage; (6) those who had received acupuncture treatment for hemiplegia, hemiparesis, and weakness owing to previous stroke; (7) those with needle phobia; and (8) pregnant or lactating female patients.

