### 2.7. Interventions

#### 2.7.1. Study Flow and Treatment Procedure

Acupuncture treatment will be performed once during the trial. The acupuncture treatment will be carried out by a practitioner with more than 2 years of clinical experience. Before the treatment procedure, the patient's basic characteristics (e.g., age, sex, body mass index (BMI), vital signs, past medical history, drug consumption, education, occupation, alcohol consumption, smoking habit, and stroke type (cerebral infarction or cerebral hemorrhage), MMSE-K, National Institute of Health Stroke Scale (NIHSS) score, and Modified Rankin Scale will be investigated.

The entire procedure will be performed over 20 minutes. After all of the preparations for treatment are complete, the participants will be asked to lie on the bed for 2–5 min to stabilize. In the verum acupuncture group, real manual acupuncture will be performed. In the three sham acupuncture groups, Park Sham Device, Streitberger's needle, or insertion- and removal-type acupuncture will be applied. Details of the acupuncture treatment are described in the Standards for Reporting Interventions in Clinical Trials of Acupuncture (STRICTA) checklist in Table 1. During the entire trail period, all the procedures of acupuncture will be carried out by one practitioner who is independent. During the procedure, a prepared visual barrier will prevent participants from viewing their arm and confirming the type of acupuncture. Immediately after the end of the procedure, a questionnaire for determining Bang's blinding index and the “Discomfort caused by acupuncture therapy” questionnaire will be administered, and the Massachusetts General Hospital Acupuncture Sensation Scale (MASS) index, by deqi sensation, will be determined (Figure 1).

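### The MASS index and discomfort score are compared by ANOVA without the sensory stratum or baseline NIHSS, which forgoes precision and leaves chance imbalance in NIHSS uncorrected

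*Protocol article*

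**What the plan says.** - **Analysis.** Section 2.11 states that the discomfort questionnaire's "five questions and MASS index will be compared by ANOVA". It names no covariate and no stratum term, and it rules out sensitivity analyses. Baseline data are used for chi-square and ANOVA comparisons between arms.
- **Rationale.** The Introduction says that "the paralyzed limbs of stroke patients have complex patterns of muscle tone, muscle strength, and sensory abnormality", and that "there could be differences in the degree of sensitivity during stitching and the discomfort felt during acupuncture treatment compared to those in healthy individuals".
- **Design.** Section 2.5: "The stratification is performed according to whether there is a sensory disturbance of the affected limb". Section 2.11 uses the same factor again: "In subgroup analysis, we will compare the values of primary and secondary outcomes in patients with sensory disturbances".
- **Baseline data.** The list in section 2.7.1 ends with "MMSE-K, National Institute of Health Stroke Scale (NIHSS) score, and Modified Rankin Scale will be investigated". Muscle tone appears in section 2.3 as an entry limit, "with a Modified Ashworth Scale (MAS) score of 2 points or less", and is not in the 2.7.1 list. No separate measure of limb strength is listed.
- **Size.** Section 2.10 plans at least 22 per group and 90 in all, taken from a study in healthy individuals, without a power calculation.

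**The concern.** If impairment of the limb can change how a needle feels, patients with different degrees of impairment may report different sensations whatever device they receive. That variation then sits in the error term of a plain ANOVA.

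The sensory stratum is balanced by design but left out of the model, so the variance it explains is not removed. NIHSS is neither stratified nor modelled, so a chance difference between a sham arm and verum carries into the comparison. The planned baseline tests may show such a difference but do not correct for it.

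This matters because the stated hypothesis is about which sham feels most like verum, and the MASS index and discomfort score measure sensation directly. For a question of similarity, imprecision is not a cautious error: a noisy, non-significant difference can be read as evidence of a good sham.

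**Working it through.** **Plan's own figure.** 4 × 22 = 88 against 90 stated, which leaves 2 patients for withdrawal (2/90 = 2.2%). There is no power, SD or effect size to reproduce, so the checks use 22 per arm and the 5% level.

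**Assumption.** R² is the share of within-arm outcome variance explained by the covariates. The document gives no value, so 0 to 0.30 is shown.

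**Precision.**
- Standard error ratio, adjusted to unadjusted: √(1 − R²).
- Equivalent patients per arm: 22/(1 − R²).
- Pairwise difference detectable with 80% power: (1.96 + 0.84) × √(2/22) × √(1 − R²), which is 0.84 SD at R² = 0.
- Power of the four-group F test: noncentral F with noncentrality 88f²/(1 − R²), on 3 and 84 degrees of freedom unadjusted, or 3 and 82 with two covariates. The effect is set at f = 0.36, where plain ANOVA has 80.0% power.

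| Assumed R² | SE reduction | Equivalent n per arm | Detectable difference (SD) | Power with two covariates |
|---|---|---|---|---|
| 0 | 0% | 22 | 0.84 | 79.95% |
| 0.05 | 2.5% | 23.2 | 0.82 | 82.1% |
| 0.10 | 5.1% | 24.4 | 0.80 | 84.4% |
| 0.20 | 10.6% | 27.5 | 0.76 | 88.7% |
| 0.30 | 16.3% | 31.4 | 0.71 | 92.7% |

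**Chance imbalance in NIHSS.** In SD units, the difference between two arms in an unstratified covariate has SD √(2/22) = 0.30, so its 95% range is about ±0.59. It exceeds 0.5 SD in either direction for a given sham against verum in 9.7% of randomisations, and for at least one of the three shams in about 23% (400,000 simulated randomisations).

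If NIHSS alone explains R², an imbalance of 0.5 SD shifts the unadjusted difference by 0.5 × √R². That is 0.16 SD at R² = 0.10 and 0.22 SD at 0.20, against a standard error of 0.30 SD. Given exactly that imbalance, the false-positive rate of an unadjusted pairwise 5% test (normal approximation) is 7.0% at R² = 0.10 and 8.8% at 0.20.

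**Validity.** Over 8,000 simulated trials per setting, with two covariates left to chance, type I error of plain ANOVA was 5.1%, 5.2% and 5.0% at R² = 0, 0.10 and 0.30. With ANCOVA it was 4.6%, 5.5% and 5.0%.

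**The stratum.** These power and error figures treat the covariates as unstratified. For a factor balanced by blocks, plain ANOVA instead overstates the standard error. The pairwise error rate is then 2 × [1 − Φ(1.96/√(1 − R²))], or 3.9% if the stratum explains 0.10 and 2.8% if it explains 0.20. That is conservative, not invalid.

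**The case against.** The strongest objection is that an unadjusted ANOVA of randomised arms is a legitimate analysis. It is unbiased over randomisations, and its error term already allows for chance imbalance. The outcomes are secondary, and Bang's blinding index is untouched. Covariates may also be specified in an analysis plan that is not shown. All of this stands, except that section 2.11 is not silent: it names the method and excludes sensitivity analyses.

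A reader might go further than the text allows in four ways.

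- **That the plan asserts that tone and strength change needle sensation.** It says only that there could be differences, and the contrast is with healthy people. That these features predict sensation among trial patients is a reasonable inference from the rationale, not a statement in it.
- **That tone and strength are already baseline data.** MAS is given only as an entry limit, which also narrows its range and so its likely explanatory power. Strength is at most reflected indirectly in NIHSS.
- **That the comparison is biased.** The conditional error rates above describe an unlucky allocation. Averaged over allocations the rate is about 5%.
- **That covariates will be chosen by baseline p-values.** The plan never proposes this.

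It is also fair that the size is conjectural. At R² of 0.10 or less the gain is modest, and an imbalance above 0.5 SD against a given sham occurs in under 10% of randomisations.

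**Conclusion.** The point holds as one of efficiency and chance imbalance on secondary outcomes, not as an error of validity. The protocol stratifies on the limb feature that bears most directly on needle sensation and records a severity score at baseline, then uses neither in the model for the outcomes that measure sensation. The stratum is the covariate best supported by the protocol, with NIHSS second.

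The size rests wholly on an assumed R²: nothing is gained at 0, about 2 to 4 power points at 0.05 to 0.10, and about 9 at 0.20. The loss if the covariates turn out not to be prognostic is negligible (80.0% to 79.95% with two covariates). With so little to lose and a plausible gain, the sponsor should make the change, though the planned test would stand without it. The point covers the MASS index and the 0–10 intensity score only. It does not extend to the questions that section 2.8.2 describes as answered yes or no.

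**What to change.** In section 2.11, state that the MASS index and the 0–10 discomfort intensity score will be analysed by ANCOVA, with group, the sensory-disturbance stratum and baseline NIHSS as prespecified terms, whatever the baseline comparisons show. Add MAS only if the screening value is kept as baseline data, in which case it should be added to the list in section 2.7.1. Report adjusted sham-minus-verum differences with confidence intervals for each of the three devices, and show the unadjusted ANOVA alongside.

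The cost is a sentence or two in 2.11 and no new measurement. The model uses two degrees of freedom of about 84, or three with MAS. The statement that no sensitivity analysis will be done needs a small edit so that it does not conflict with presenting the unadjusted result.
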